#### The Intervention Condition

A CRC will assist study participants assigned to the intervention group with downloading FiberMore onto their smartphones and input the initial fiber goal of the study participants to the backend system (refer to Table 2 for determination of the initial goal). The CRC will also assist the study participants to identify 1 barrier on increasing fiber intake and its corresponding solution via the “Barrier and Solution” chatbot within FiberMore. The CRC will also provide guidance and demonstration on using the intervention features of FiberMore.

The CRC will give study participants a handout on the benefits of increasing fiber intake as well as general tips and examples about eating more fiber. As some study participants depend on their family for meal preparation, the CRC will encourage the study participant to share the educational handout with their family members and communicate the weekly fiber goal as well as the feedback obtained from FiberMore with their family or person preparing their meals.

On the first three days during week 10, at 11 AM, study participants will receive an SMS text message containing a survey link for a TPB questionnaire (via Jotform). On day 1 of week 10, study participants will receive a TPB questionnaire about increasing fiber intake. On day 2, they will receive a TPB questionnaire about reducing salt intake. On day 3, they will receive a TPB questionnaire about reducing saturated fat intake. Study participants are required to complete these surveys at home or any convenient location with an internet connection.

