#### The Control Condition

After randomization, the control group will receive an educational handout on salt intake reduction as well as a paper diary to record their efforts in reducing salt intake. They are encouraged to record any small effort to reduce salt intake in the diary on a daily basis. They will also receive web-based educational information via SMS text message once during week 4 and once during week 8 (see Figure 4). On the last day of week 10, the control group will receive SMS text message reminders from the research office to use MealLog to log their meals for 14 days during week 11 and week 12 (see Figure 5).

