#### Study Events

This study includes 5 events (E0-E4), a 2-week run-in period, a 12-week intervention period, and a 12-week observation period. Study participant experience and data collected in different stages of the study are described in Table 3.

**Table 3. T3:** Study events spanning approximately 26 weeks.

Event	Time	Key activities	
E0	Preliminary study enrollment	Participant experience: obtain consent to participate in study. Data collected: Patient background^a^, vital signs^b^, hematological tests^c^, biochemical tests^d^, urinalysis^e^, medication status survey, and the transtheoretical model (TTM) questionnaire for dietary behavior change^f^.	
Run-in period	From E0 for 2 weeks	Participant experience: Log meals with MealLog app Data collected: Number of days with at least 2 logged eating occasions (main meals or snacks), total fiber intake per day (grams), average fiber intake (excluding days with only 0 or 1 logged meal), theory of planned behavior (TPB) questionnaire for dietary fiber intake^g^, TPB questionnaire for salt intake^g^, and TPB questionnaire for saturated fat intake^g^.	
E1	At the time of official study enrollment	Intervention group: Participant experience: Download FiberMore and receive educational handout on dietary fiber intake. Data collected: Medication status and system defects.	
		Control group: Participant experience: Receive educational handout on salt reduction. Data collected: Medication status and system defects.	
Intervention period	From E1 for 12 weeks	Intervention group: Participant experience: Interact with FiberMore. Data collected: The number and percentage of days fiber goal is met out of 7 days, the number and percentage of implemented coping strategies per week, the average estimate of fiber intake per day (excluding days with only 0 or 1 logged meal), and the average estimate of energy intake per day (excluding days with only 0 or 1 logged meal).	
		Control group: Participant experience: Record salt reduction efforts in a paper diary (sham intervention), receive 1-time educational weblink on salt reduction via an SMS text message during week 4 and week 8, and use MealLog to log meals during week 11 and week 12. Data collected: During week 11 and week 12—the average estimate of fiber intake per day (excluding days with only 0 or 1 logged meal) and the average estimate of energy intake per day (excluding days with only 0 or 1 logged meal).	

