### Statistical Analysis Plan

In this study, we define 3 analysis populations: the full analysis set (FAS), the per protocol set (PPS), and the safety analysis set (SAS). The FAS is defined by all the study participants who had at least one primary outcome or secondary outcome obtained after randomization. We will follow the intention-to-treat (ITT) principle and analyze data based on the assigned group in the FAS analysis. The PPS is the FAS population with exclusion of patients who were found to have serious violations of the provisions of the research protocol:

Violation of inclusion and exclusion criteriaStudy participants who log fewer than 2 meals per day on more than 7 days within any of the following 2-week intervals during the intervention period: Weeks 1‐2, 3‐4, 5‐6, 7‐8, 9‐10, 11‐12, or 13‐14.In the event of a medical condition that makes dietary fiber intake inappropriate for the study participants,

Major deviations from other provisions of the study protocol will be assessed through a blinded review process. The blinded review will be conducted according to the following procedures: assessment of whether individual participants or specific measurement data should be excluded from the PPS or FAS; evaluation of participants with significant protocol deviations to determine whether exclusion is warranted; and examination of efficacy outcomes, including consideration of potential variable transformations and identification of outliers.

The safety analysis set is the set of all patients who used either MealLog or FiberMore at least once after randomization. In the safety analysis using the SAS, we will analyze data based on the intervention actually used by patients regardless of allocation. The FAS will be the primary analysis population, and the PPS will provide supportive results. All safety analyses will be conducted in the SAS. Data on patients’ characteristics will be presented as mean, minimum, SD, 25th percentile, median, 75th percentile, and maximum for continuous variables and as frequency and proportion for categorical variables.

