We will also calculate the percentage of responses for each option on the Likert scale and for the “Yes or No” scale in “Survey on participants’ satisfaction and perceived usefulness of the intervention” at the end of the intervention period for both intervention group and control group. For the “Survey on intention to improve eating habits using a Generative AI-enabled app”, we will calculate the percentage of responses for each option on the Likert scale at the end of the observation period for the intervention group.

As part of our exploratory analysis, we will assess the reliability of the TPB questionnaire using the Cronbach α coefficient. Additionally, we will conduct multivariate regression analyses to examine various associations related to the TPB constructs. Specifically, we will investigate the relationship between changes in intention (INT) to increase fiber intake and changes in fiber intake outcomes both between and within groups. Furthermore, we will analyze the associations between changes in attitude (ATT), subjective norms (SN), and PBC with changes in intention to increase fiber intake, as well as the relationship between changes in PBC and changes in fiber intake outcomes at both the between-group and within-group levels. The impact of the intervention on INT via ATT, SN, and PBC will be evaluated through mediation analysis.

We will calculate the frequency and weekly percentages of the following measurements during the intervention period in the intervention: number and percentage of days fiber goal is met out of 7 days, the number and percentage of implemented solutions in a week, the average weekly fiber change in the intervention group from run-in, and the average weekly energy change in the intervention group from run-in. We will also evaluate the effects of changes in dietary fiber intake on changes in BMI and HbA_1c_ using the Pearson correlation test and simple regression analysis.

We will perform a statistical analysis of safety outcomes by calculating the number and percentage of individuals who experience adverse events during run-in, intervention, and observation periods. During the intervention and observation periods, data will be compiled separately for the intervention and control group, and the percentages will be compared between groups using the Fisher exact test.

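### Safety set entry depends on app use after randomization, which is immediate for FiberMore but not scheduled for controls until week 11, so the adverse-event comparison can be biased in either direction

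*Protocol article*

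**What the plan says.** The Statistical Analysis Plan section defines the set: "The safety analysis set is the set of all patients who used either MealLog or FiberMore at least once after randomization". It then fixes how patients are grouped, "we will analyze data based on the intervention actually used by patients regardless of allocation", and rules out any other population for safety: "All safety analyses will be conducted in the SAS".

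The two arms meet an app at different times:

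- **Intervention arm.** The Intervention Condition section states: "A CRC will assist study participants assigned to the intervention group with downloading FiberMore onto their smartphones". The coordinator also helps each participant work through one barrier and its solution in the FiberMore chatbot. Table 3 places this at E1: "Download FiberMore and receive educational handout on dietary fiber intake".
- **Control arm.** The Control Condition section describes what is given once patients have been allocated: "the control group will receive an educational handout on salt intake reduction as well as a paper diary to record their efforts in reducing salt". Web content follows by SMS in weeks 4 and 8. The only app task comes after a reminder on the last day of week 10, "to use MealLog to log their meals for 14 days during week 11 and week 12".

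The safety comparison is in the Secondary Outcomes Analysis section: "During the intervention and observation periods, data will be compiled separately for the intervention and control group, and the percentages will be compared between groups". The planned test is Fisher's exact. The Secondary Outcomes section says adverse events are assessed by interviewing patients. Ethical Considerations says that data gathered before a post-randomization withdrawal are kept.

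**The concern.** A safety set should be fixed by something that happens at or near the start of exposure and in the same way in both arms. Here it is fixed by an event after randomization that normally comes on day 0 in one arm and not before week 11 in the other. For controls, membership therefore depends in practice on about ten weeks of retention followed by at least one log. For FiberMore participants it depends on almost nothing.

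There is also a mismatch of content. The control intervention is salt education plus a paper diary. MealLog is the measuring tool, used by everyone in the run-in and by controls again in weeks 11 and 12. Opening it does not show that a person received the sham, so grouping by the intervention actually used has no clear meaning for this arm when use is judged by app.

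At stake is the only planned between-group safety test, in a trial that names safety among the things it will inform.

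**Working it through.** The protocol gives no numerical figure on this point, so there is none to reproduce. The check compares the entry rule with the schedule and then illustrates the size.

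**Step 1: when each arm can qualify**

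| | FiberMore | Control |
|---|---|---|
| Given at E1 | FiberMore, fiber handout | Salt handout, paper diary |
| Weeks 1–10 | FiberMore daily | Diary; SMS content in weeks 4 and 8 |
| Weeks 11–12 | FiberMore daily | MealLog, 14 days |
| First scheduled app use after randomization | E1 | Week 11 |

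The control arm's first scheduled use comes after 10 of 12 intervention weeks: 10/12 = 83% of the period.

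**Step 2: who is left out**

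- A control who withdraws in weeks 1–10 without an unprompted log is outside the set, even though data to that point are kept.
- A control who completes follow-up but does not log in weeks 11–12 (or at any other time after randomization) is also outside. That same person is in the full analysis set, which needs only one primary or secondary outcome after randomization, for example HbA1c at week 12. The safety set would then omit someone counted for efficacy.
- FiberMore participants with the same histories are in the set from E1.

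**Step 3: size, by illustration**

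Inputs:
- n = 36 per arm. The Results section reports 72 randomized and the allocation ratio is 1:1, so 72/2 = 36. Actual arm sizes are not stated.
- e = 8 participants with an event in each arm, 8/36 = 22.2%. This is an assumption; the document gives no event rate.
- k = excluded controls who had an event; m = excluded controls who had none. Both are assumptions.

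Observed control rate = (e − k)/(n − k − m). The FiberMore rate stays at 8/36 = 22.2%.

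| Excluded controls | All had an event (m = 0) | Fisher p against 8/36 | None had an event (k = 0) |
|---|---|---|---|
| 0 | 8/36 = 22.2% | 1.00 | 8/36 = 22.2% |
| 1 | 7/35 = 20.0% | 1.00 | 8/35 = 22.9% |
| 2 | 6/34 = 17.6% | 0.77 | 8/34 = 23.5% |
| 4 | 4/32 = 12.5% | 0.35 | 8/32 = 25.0% |

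The two rate columns are the extremes for a given number excluded. If those excluded have the same risk as the rest, the rate does not move: excluding 9 controls, 2 of them with an event, gives (8 − 2)/(36 − 9) = 6/27 = 22.2%.

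**The case against.** The strongest reply is that few controls will be affected. One log is enough. Everyone randomized has already logged at least two eating occasions a day on at least seven run-in days. Controls are reminded by SMS before week 11, and payment follows completion of the 24 weeks. The Sample Size Consideration section expects little or no dropout, citing an earlier study by the same team with the same structure. All of this stands, and it limits the likely size. It does not remove the asymmetry in the rule, and low dropout does not cover a control who stays but does not log.

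A reader might infer more than the documents support:

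- **That controls have no app before week 11.** MealLog is installed at consent, and nothing says it is removed or locked. What is missing is scheduled use, not the app.
- **That the bias makes FiberMore look less safe.** That follows only if excluded controls had more events than the rest. If event-free controls are the ones who do not log, the control rate rises instead. The documents do not say which is more likely.
- **That a large gap between arms is to be expected.** The larger gaps in the illustration need several exclusions, every one of them a case.
- **That control harms are hidden.** Events are still collected and retained. What is affected is who enters the comparison.
- **That Table 3, which lists no adverse-event item, shows that collection is missing.** The article says interviews are done, and their timing is a detail it may leave to the full protocol.

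**Conclusion.** The point holds as a defect in the definition of the safety set. It is certain from the text that entry relies on an event scheduled about ten weeks later in one arm, and on a tool that does not measure exposure to the sham. The between-arm adverse-event comparison can therefore be biased in either direction.

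The size cannot be known in advance. With an assumed 36 per arm and 22.2% with events, two excluded controls move the control rate to somewhere between 17.6% and 23.5%, and four to between 12.5% and 25.0%. There is no bias if none are excluded or if those excluded carry the same risk as the rest. Given the dropout the protocol expects, a small effect is more plausible than a large one. The FiberMore arm's own rate is essentially unaffected. The change is still worth making because the rule is explicit, no other safety population is planned, and the correction needs no new data.

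**What to change.** Replace the definition with one along these lines: the safety set comprises all randomized participants who received any component of their arm at E1 (FiberMore installed, or the salt handout or diary given), analysed by the condition received, with adverse events counted from E1. Remove app use as the entry rule.

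This costs one sentence in the analysis plan. The events are already collected by interview, and the E1 materials are handed out under the existing procedure, so no visit or form has to change. The sentence should be settled before any safety data are compared by arm.

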### Primary Outcome Analysis

We will perform analysis of covariance on the change in dietary fiber intake from the time of run-in to the end of the intervention period, with dietary fiber intake from the time of run-in as the covariate. The change in dietary fiber from the time of run-in and at the end of the intervention period will be calculated as ([average dietary fiber over week 11 and 12]-[average baseline dietary fiber during the run-in]). The estimated mean change in each group and its 2-sided 95% CI will be calculated. Additionally, the estimated difference between groups and its 2-sided 95% CI will be calculated.

To ensure reliable estimates of fiber intake, days with only 0 or 1 logged meal will be excluded from the analysis.

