#### Run-in Period

During the run-in period, preliminarily enrolled study participants will use MealLog to log their meals so that the researchers can assess their average baseline fiber intake. A research co-investigator will contact the study participants via SMS text messages if participants do not log any meals or if only 1 meal is logged for 3 days consecutively since the start of the run-in period.

To be eligible for official study enrollment, study participants need to log at least 2 eating occasions (either main meals or snacks) in app per day for at least 7 days during the nominal 14-day run-in period and have an average baseline fiber intake of less than 20 g per day (after excluding days with 0 or 1 logged meal per day).

On the first 3 days of the run-in, at 11 AM, preliminarily enrolled study participants will receive an SMS containing a survey link for the TPB questionnaire (via Jotform). On day 1 of the run-in, study participants will receive a TPB questionnaire on increasing fiber intake. On day 2 of the run-in, they will receive a TPB questionnaire on reducing salt intake. On day 3 of the run-in, they will receive a TPB questionnaire on reducing saturated fat intake. Study participants are required to complete these surveys at home or at any convenient location with an internet connection. If the questionnaire submissions are not received by the 3rd day of the week, another SMS text message will be sent on the 4th day as a reminder to complete the missing questionnaire.

After completion of the run-in period, study participants will be contacted by the research office about their official study enrollment status.

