#### Official Study Enrollment and Randomization

Randomization will be conducted using a dynamic allocation method based on minimization, with an allocation ratio of 1:1. The allocation adjustment factors will include the baseline dietary fiber intake during run-in (under 10 g, 10 g and above), sex (male and female), and HbA_1c_ level on the date of consent (less than 8.5% and 8.5% or higher). Random allocation will be performed online using the INDICE cloud system provided by the University Hospital Medical Information Network (UMIN). After randomization, a CRC will explain the details of the intervention according to the study participants’ allocated group (intervention or control). Participants are blind to their group.

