### Sample Size Consideration

The primary outcome is the difference between the intervention group and the control group in the change in mean daily dietary fiber intake from the time of study enrollment to the end of the intervention period. We desired to detect a between-group difference in the mean change of 7 g of dietary fiber, drawing from a meta-analysis, which demonstrated a 9% risk reduction of cardiovascular disease events for 7 g increase in daily dietary fiber intake [47]. A previous RCT reported a 7.9 g/day increase in fiber intake at 3 months in the high-fiber group, supporting the use of a 7 g/day between-group difference as a realistic and meaningful target [33].

Based on the findings from a previous nutritional intervention research in Japan [48], we assumed a common SD of 9.85 g for the difference in dietary fiber change across both groups. Using a 2-sided significance level of 5% and a power of 80%, the required sample size calculated based on an independent *t* test is 33 participants per group. A study conducted in a similar population, which followed a similar study structure with a 2-week run-in phase, a 12-week intervention phase, and a subsequent 12-week observation phase by our research team showed minimal to no dropout throughout the study duration [49]. Nevertheless, as a conservative estimate to account for potential attrition, we aimed to enroll a minimum of 70 participants. The 2-week run-in phase also ensures that we enroll the participants who are able to use the app as instructed, thus minimizing drop-out risk.

Based on the findings from previous studies implemented in our research lab, we estimate a 10% dropout rate between preliminary and official study enrollment. Therefore, the target recruitment number for the preliminary study enrollment has been set at 77 participants.

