### Secondary Outcomes Analysis

We will perform analysis of covariance on the change of HbA_1c_ from the time consent is obtained to the end of the intervention period (at 12 weeks) or the end of the observation period (at 24 weeks), using the measurements at the time consent is obtained as covariates. The estimated mean change in each group and its 2-sided 95% CI will be calculated. Additionally, the estimated difference between groups and its 2-sided 95% CI will be calculated. The proportion of HbA_1c_ less than 7% at week 12 (E3) and week 24 (E4; or point of discontinuation, if earlier) will be compared between groups by the Fisher exact test.

The change from baseline in the clinical laboratory test values stated below at week 12 (E3) and week 24 (E4) (or point of discontinuation, if earlier) will be analyzed as the secondary outcomes:

 Weight (kg) BMI (kg/m^2^) Systolic and diastolic blood pressure (mmHg) Estimated glomerular filtration rate (ml/min/1.73 m^2^) Fasting blood glucose (mg/dL) Low-density lipoproteincholesterol (LDL-C; mg/dL) High-density lipoproteincholesterol (HDL-C; mg/dL) Triglyceride (mg/dL)

The percentages of participants at each stage of the transtheoretical model (TTM) stage of change will be calculated for both groups at the end of the intervention period (week 12) and the end of the observation period (week 24) were compared between groups using the Cochran-Mantel-Haenszel test.

Between-group changes in all TPB survey elements for dietary fiber, salt, and saturated fat intake (attitude, subjective norms, PBC, and intention) will be analyzed from the time of run-in to the end of 10 weeks, and to the end of the observation period (24 weeks), using repeated measures ANOVA with time (Week 1, Week 10, and Week 24) as a within-subjects factor and group (control vs intervention) as a between-subjects factor.

Changes in diabetes medications since consent acquisition at the end of the intervention period (at 12 weeks) and at the end of the observation period (at 24 weeks; classified as intensified, unchanged, and weakened) will be calculated for each group and compared between groups using the Cochran-Mantel-Haenszel test. The proportion of new medications added will be compared between groups by the Fisher exact test.

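### The primary ANCOVA omits two of the three minimization factors, and the TPB analysis uses the pre-randomization score as an outcome; the first costs little and only conditionally, the second costs definite precision on exploratory outcomes

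*Protocol article*

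**What the plan says.** Protocol article, Official Study Enrollment and Randomization: allocation is 1:1 by minimization. "The allocation adjustment factors will include the baseline dietary fiber intake during run-in" (cut at 10 g), together with sex and HbA1c on the date of consent (cut at 8.5%).

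Primary Outcome Analysis: the change in fiber from run-in to weeks 11 and 12 is analysed by ANCOVA "with dietary fiber intake from the time of run-in as the covariate". Sex and HbA1c are not mentioned. Under Secondary Outcomes Analysis, the HbA1c ANCOVA carries only HbA1c at consent, so run-in fiber and sex are absent there.

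The same section analyses the TPB elements "using repeated measures ANOVA with time (Week 1, Week 10, and Week 24) as a within-subjects factor" and group as the between-subjects factor. The first TPB survey is taken before allocation: "On the first 3 days of the run-in, at 11 AM, preliminarily enrolled study participants will receive an SMS containing a survey link" (Run-in Period). The later surveys are in week 10 and at E4 (week 24). Footnote b of Table 4 defines the TPB outcome as the difference in change from run-in to week 10 and to week 24.

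**The concern.** Minimization makes the arms more alike on its factors than simple randomization would. If a factor predicts the outcome, the treatment estimate varies less from trial to trial. A model that omits the factor leaves its contribution in the residual variance and reports a standard error that does not reflect this gain. The result is a conservative test and an interval wider than it needs to be, in a trial that has randomized 72 people.

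The TPB issue is different in kind. The run-in score precedes allocation, so no treatment effect can exist there. Treating it as a level of the outcome amounts to analysing simple change from run-in, which is less precise than adjusting for the run-in score. The plan uses baseline-adjusted ANCOVA for fiber and HbA1c but not here, although the TPB constructs are the mechanism by which the intervention is meant to act.

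**Working it through.** **1. The plan's own figure.** Inputs from Sample Size Consideration: a "between-group difference in the mean change of 7 g of dietary fiber", two-sided 5% level, 80% power, and "we assumed a common SD of 9.85 g for the difference in dietary fiber change across both groups". The exact noncentral-t calculation gives 81.1% power at 33 per group and 79.9% at 32. The statement that "the required sample size calculated based on an independent *t* test is 33 participants per group" is reproduced. It rests on an unadjusted test and takes no credit for any covariate.

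**2. Primary model, by formula.** Let R² be the share of residual variance, given run-in fiber, explained by sex and HbA1c. The documents do not give it; 0 to 0.10 is assumed. For simplicity 9.85 g is used as the residual SD of the stated model.

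Half-width of the 95% CI = t(0.975, df) × 9.85 × √(1 − R²) × √(2/n), with n = 33 per group.

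Stated model (no adjustment for the two factors): df = 2×33 − 3 = 63; 1.998 × 9.85 × √(2/33) = 4.85 g; power at 7 g is 81.1%.

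With sex and HbA1c added, df = 61:

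| Assumed R² | Half-width (g) | Power at 7 g | Excess width of stated model |
|---|---|---|---|
| 0 | 4.85 | 81.1% | none |
| 0.02 | 4.80 | 81.9% | about 1% |
| 0.05 | 4.73 | 83.0% | about 2.5% |
| 0.10 | 4.60 | 85.0% | about 5% |

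At R² = 0 the two lost degrees of freedom widen the interval by less than 0.1%. With 36 per group (72 randomized, an equal split and no losses assumed), the same calculation at R² = 0.10 gives 4.63 g against 4.40 g, and 84.4% against 87.9% power.

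**3. Primary model, by simulation under minimization.** 66 participants, 4,000 trials per setting, three-factor minimization with an assumed biased-coin probability of 0.8, and R² = 0.10:

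| | Run-in fiber only | Plus sex and HbA1c stratum |
|---|---|---|
| SD of the estimate at 7 g (g) | 2.32 | 2.31 |
| CI half-width at 7 g (g) | 4.85 | 4.61 |
| Type I error | 4.4% | 5.1% |
| Power at 7 g | 82.7% | 85.2% |

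The two estimators have almost the same true spread, so the loss lies in the reported standard error. The Monte Carlo standard error of a 5% rate is √(0.05 × 0.95/4000) = 0.34 points, so 4.4% alone is only weak evidence of conservatism. The interval widths show it more clearly.

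**4. TPB.** Let rho be the correlation between the run-in and follow-up scores, with equal variances over time. It is not in the documents; 0.3 to 0.8 is assumed. Per unit of score variance:

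- change from run-in: 2(1 − rho)
- follow-up score adjusted for run-in score: 1 − rho²
- ratio: 2(1 − rho)/(1 − rho²) = 2/(1 + rho)

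This gives 1.54 at rho 0.3, 1.33 at 0.5, 1.18 at 0.7 and 1.11 at 0.8. It exceeds 1 for every rho below 1.

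Where ANCOVA has 80% power, the change contrast has approximately Φ(2.802/√ratio − 1.960). At rho 0.5: 2.802/1.155 = 2.427, less 1.960 = 0.467, which is 68%. The corresponding figures are 62% at rho 0.3 and 73% at rho 0.7.

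**The case against.** On the primary model, no evidence in the document shows that sex or HbA1c predicts change in fiber beyond run-in fiber, which is the outcome's own baseline and is already in the model. A reader might infer that the primary interval is certainly too wide, or that the trial loses planned power. Neither is supported: the loss is nil if the factors are not prognostic, any error is conservative, and the sample size assumed no adjustment. This part of the objection stands.

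On TPB, a reader might infer that the planned ANOVA cannot answer the stated outcome, or that its conclusion would rest on a group main effect diluted by a visit without treatment. The text supports neither. It speaks of between-group changes from run-in to each later time, and the named model can yield those contrasts. It never says that inference rests on the main effect. The method is valid, and the outcomes are secondary and declared exploratory. What remains is that the contrasts are less precise than they need be.

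It may also be tempting to say that the Week 1 survey does not exist. The first surveys go out on days 1 to 3 of the run-in, and the sentence in question itself refers to the run-in. The label is ambiguous, because the Figure 2 caption counts week 1 as the start of the intervention, but no visit is missing.

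**Conclusion.** The point holds at modest size. For the primary outcome, the model does not reflect the allocation. Under an assumed R² of 0 to 0.10, its interval is about 0 to 5% wider than needed and power is 0 to 4 points lower by formula (2.5 points in the simulation at 0.10). The estimate is not biased, and the planned 80% power is not put at risk. How large the loss is depends on a quantity that the documents do not give.

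For TPB, the loss does not depend on whether sex or HbA1c is prognostic: 11 to 54% more variance than ANCOVA for rho from 0.8 to 0.3. It affects exploratory results only. Both are worth correcting because the remedy uses data already collected and costs almost nothing.

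**What to change.** - Add sex and HbA1c at consent to run-in fiber in the primary ANCOVA, stating whether HbA1c enters as a continuous value or by stratum.
- Add run-in fiber and sex to the HbA1c ANCOVA. Where other change outcomes are analysed by ANCOVA, include the three minimization factors beside the outcome's own baseline. The article names no model for those outcomes.
- Analyse week 10 and week 24 TPB scores by ANCOVA, or by a mixed model on those two visits, with the run-in score as covariate and a separate group contrast at each time.
- Replace the label Week 1 with run-in.

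The cost is two degrees of freedom in the primary and HbA1c models and up to three in the others. No new data are needed. Recruitment has ended and the primary model is published, so the change needs a dated, documented amendment before any unblinded analysis. The fiber-only ANCOVA can be kept as a sensitivity analysis.
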